Current evidence suggests that combined therapy typically enhances efficacy compared to monotherapy, though study conclusions remain inconsistent.Chen et al. [17]observed significantly improved vascular vasomotor function in the combined therapy group via transcranial Doppler ultrasonography, linked to optimized hippocampal activation patterns and a bidirectional beneficial cycle between vascular and cognitive functions. Notably, Kolskar et al. [18] reported no additional benefits of tDCS-CCT combinations over CCT alone in high-reliability fMRI-based brain activation analyses.Meanwhile, studies confirm significant differences in clinical outcomes between combined strategies.Naro et al. [19]found both concurrent tDCS-RAGT and sequential RAGT-then-tDCS interventions in stroke patients significantly improved balance (p < 0.001) and moderately enhanced gait endurance (p = 0.04), with the sequential approach showing particularly sustained effects—contradicting Leon’s null findings [20].Current investigations into tDCS-CCT combinations highlight potential cognitive benefits, yet their efficacy remains inconsistent [21].A meta-analysis confirmed significant improvements in working memory with CCT in stroke patients, but there were insufficient tDCS studies for analysis, and meta-regression identified no significant moderators.Given that tDCS and CCT exhibit complementary mechanisms of action and that controversy exists regarding the efficacy of combined tDCS at different time sequences., we will propose combining these interventions to address cognitive impairments in stroke patients [22].

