Given the significant gap in research on combined tDCS-CCT intervention strategies, particularly the lack of systematic exploration into the differential effects between simultaneous and sequential intervention modes, this study will investigate the cognitive intervention effects of tDCS in stroke patients undergoing CCT. The primary objective will be to compare efficacy differences across various temporal combinations of tDCS-CCT therapies to identify the optimal synergistic protocol. Rooted in the theoretical framework linking tDCS-mediated cerebral hemodynamic modulation to cognitive enhancement, the study will specifically examine the association between prefrontal cortical oxygen metabolism and cognitive improvement. Functional Near-Infrared Spectroscopy (fNIRS) will be used to dynamically monitor pre- and post-treatment hemodynamic parameters in the prefrontal cortex, aiming to elucidate the neurophysiological mechanisms underlying cognitive recovery through the lens of neurovascular coupling.

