### Sample size estimation

Prior to study initiation, we will perform sample size estimation using G*Power 3.1.9.7 (Heinrich Heine-Universität Düsseldorf, Düsseldorf, Germany). The primary outcome will be the MoCA score, and the effect-size parameter will be set at Cohen’s f = 0.708, as reported in a peer-reviewed publication [17]. The statistical model will be a linear mixed model testing the group × time interaction. The following settings will be used: power = 0.95, α = 0.05, four groups, three repeated measurements (baseline, post-treatment, and follow-up), and a within-subject correlation of 0.30 (reflecting an expected increase in between-subject variability at follow-up). The software will indicate that a total of 48 participants will be required. Anticipating a 20% dropout rate, we will divide 48 by 0.8 and round up to the nearest multiple of four, resulting in a planned recruitment of 60 participants (15 per group).

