### Statistical methods

#### Clinical data analysis.

Statistical analyses will be conducted using SPSS 26.0, with a two-tailed significance level of p < 0.05. Categorical variables will be presented as frequencies and percentages, and compared using chi-square tests. Continuous variables will be assessed for normality using the Shapiro-Wilk test; normally distributed data will be reported as mean±SD, and non-normally distributed data as median [IQR].For repeated measures (e.g.,cognitive assessments at multiple timepoints), linear mixed models (LMM) will be used to include covariates (e.g., age, baseline scores, education level) and manage missing data. Between-group comparisons at individual timepoints will be conducted using one-way ANOVA for normally distributed data or Kruskal-Wallis tests for non-normal data, with multiple comparisons adjusted using the false discovery rate (FDR) method. Correlations will be analyzed using Pearson’s correlation for normally distributed data and Spearman’s correlation for non-normal data.The primary outcome analysis will be conducted on an intention-to-treat (ITT) basis [26]. Missing data will be addressed using complete case analysis if the missing rate is less than 5%, or multiple imputation if the missing rate is 5% or higher [27].

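### The sample size of 48 at 95% power does not follow from the stated repeated-measures inputs, and that power does not apply to the timing comparison that is the primary objective

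*Protocol article*

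**What the plan says.** The protocol article, under 'Sample size estimation', names G*Power 3.1.9.7, takes MoCA as the outcome and specifies a linear mixed model testing group × time. The settings are "power = 0.95, α = 0.05, four groups, three repeated measurements (baseline, post-treatment, and follow-up"), with a within-subject correlation of 0.30. On the effect size it says "the effect-size parameter will be set at Cohen’s f = 0.708, as reported in a peer-reviewed publication [17"]. The result is "The software will indicate that a total of 48 participants will be required". A 20% dropout allowance then takes this to 60, or 15 per arm.

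The Introduction sets the aim: "The primary objective will be to compare efficacy differences across various temporal combinations of tDCS-CCT therapies". It describes reference 17 in one sentence, as having found "significantly improved vascular vasomotor function in the combined therapy group via transcranial Doppler ultrasonography". No MoCA difference, MoCA SD or timing effect is given anywhere. 'Study design' calls the trial exploratory.

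**The concern.** Two things do not fit together. First, f = 0.708 is very large, and a repeated-measures interaction test at that f should need far fewer than 48 people. Either the inputs or the output are misdescribed. Second, the test that was powered compares four arms including sham, whereas the question is which of three active timings is best. If all three active arms beat sham equally, the four-arm test could have full power while every timing contrast is zero.

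At stake is what the 95% means to someone reading the results. Stated without qualification, it can be taken to cover the timing comparison, and the protocol gives no figure for that comparison.

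**Working it through.** **Inputs.** From 'Sample size estimation': f = 0.708 (f² = 0.5013), α = 0.05, power 0.95, k = 4 groups, m = 3 measurements, ρ = 0.30, 20% dropout. From 'Clinical data analysis': tests are planned "with a two-tailed significance level of p < 0.05"; the omnibus F test is non-directional in any case.

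**Step 1: the stated model.** Group × time interaction, df1 = (4 − 1)(3 − 1) = 6, df2 = 2(N − 4), power from the noncentral F. The article does not say which effect-size option was chosen, so all three are shown.

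| G*Power option | λ | Smallest N for 0.95 | As a multiple of 4 | Power at N = 48 |
|---|---|---|---|---|
| Default | f²·N·m/(1 − ρ) = 2.148N | 14 (0.962; N = 13 gives 0.939) | 16 (0.986) | > 0.9999 |
| Cohen | f²·N·(m − 1) = 1.003N | 25 | 28 | 0.9999 |
| SPSS | f²·(N − 4)(m − 1) = 1.003(N − 4) | 28 | 28 | 0.9996 |

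None gives 48. The repeated-measures between-groups test gives 24 and a one-way ANOVA gives 40. 'Interventions' implies four MoCA time points rather than three; with m = 4 the interaction needs 12 to 24, so this does not explain 48 either.

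**Step 2: where 48 can come from.** G*Power's 'ANOVA: fixed effects, special, main effects and interactions' uses λ = f²·N and df2 = N − groups. With numerator df 6 and four groups:
- N = 48: λ = 0.5013 × 48 = 24.06, df 6 and 44, power 0.9503.
- N = 47: power 0.945.

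So 48 is reproduced exactly. That module treats all observations as independent and has no field for ρ or for repeated measures.

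**Step 3: dropout.** 48/0.8 = 60, already a multiple of four. Correct.

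**Step 4: what f = 0.708 means.** If one arm differs from the other three by δ SD at both post-baseline visits, the default-scale interaction f is δ·√(3/16 × 2/9) = 0.204δ, so δ = 0.708/0.204 ≈ 3.5 SD. With two arms against two it is 3.0 SD. On the Cohen scale the two figures are 2.4 and 2.1 SD. Read as a one-way f at a single visit, two arms against two need 2 × 0.708 = 1.42 SD.

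**Step 5: the timing contrasts.** The documents give no timing effect, so 0.5 and 0.8 SD are assumed. Take 12 completers per arm, baseline adjustment and ρ = 0.30 between all visits. Then λ = (d/σ)²·n/2 with df 1 and 48 − 4 − 1 = 43.
- Single visit: σ = √(1 − 0.3²) = 0.954.
- Average of two post-baseline visits: σ = √((1 + 0.3)/2 − 0.3²) = √0.56 = 0.748.

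| | Single visit | Average of two visits |
|---|---|---|
| λ at 0.5 SD | 0.25/0.91 × 6 = 1.65 | 0.25/0.56 × 6 = 2.68 |
| Power at 0.5 SD | 0.24 | 0.36 |
| λ at 0.8 SD | 0.64/0.91 × 6 = 4.22 | 0.64/0.56 × 6 = 6.86 |
| Power at 0.8 SD | 0.52 | 0.73 |
| Detectable at 80% power, α = 0.05 | 1.12 SD | 0.88 SD |
| Detectable at 80% power, α = 0.05/3 | 1.30 SD | 1.02 SD |

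**The case against.** The strongest reply is that 48 is probably genuine software output. Step 2 supports this, and a reader who inferred that no G*Power setting gives 48, or that the number is an arithmetic slip, would be wrong. What remains is that the paragraph describes a repeated-measures calculation with ρ = 0.30, and the setting that returns 48 is not one. Since the article names no module, even this explanation is an inference.

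The second reply is that the mismatch is conservative. This stands for the test as described: on every repeated-measures option tried, f = 0.708 needs fewer than 48. A reader might infer that the trial is too small for its stated f; it is not. The reply does not extend to the timing contrasts, for which the protocol assumes no effect.

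Third, a reader might infer that timing differences cannot reach f = 0.708. The documents do not support that. They do not say which contrast or outcome in reference 17 produced the value, and the SD equivalents range from 1.4 to 3.5 depending on scale and pattern. What can be said is that nothing in the article justifies 0.708 as a timing effect.

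Fourth, the trial is labelled exploratory, claims no equivalence, and says larger trials will be needed. That softens the consequence: misreading of a null result is a risk, not something the protocol does. It does not make an unqualified 95% correct. Nor does it allow the inference that the sample size was set by feasibility, since the article presents it as calculated.

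**Conclusion.** The point holds as a reporting error in a figure that readers will rely on. The stated model and inputs require 16 or 28 participants, not 48, and the 95% power does not describe the timing comparison. For pairs of arms with 12 completers each, power is about 0.24 to 0.36 at 0.5 SD and 0.52 to 0.73 at 0.8 SD, according to whether one visit or the average of two is used.

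The reproduction in Steps 1 to 3 uses only the article's inputs; the choice of effect-size option is open and is shown as a range. The timing figures rest on assumed differences, equal variances, a common correlation of 0.30, 20% dropout spread evenly over arms, and Bonferroni adjustment as a simple stand-in for the planned false discovery rate method. None of this calls for a different number of patients.

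**What to change.** Keep 60 patients and rewrite the paragraph.

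1. Do one of two things. Either name the G*Power module, effect-size option and inputs that give 48, and remove the claim that this is a repeated-measures calculation with ρ = 0.30; or restate the calculation for the stated model and report the number it gives.
2. In both cases, state that the 95% power does not apply to the contrasts between timings.
3. Give the pairwise difference detectable with 80% power at 12 completers per arm: about 1.1 SD at a single visit (1.3 SD with Bonferroni adjustment for three comparisons), or about 0.9 SD (1.0 SD) for the average of two post-baseline visits.
4. Say that a non-significant timing contrast will not be read as equivalence.

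The cost is one rewritten paragraph and a less favourable stated figure.

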### Interventions

All participants will receive five sessions per week for two weeks, totaling 10 sessions. Adverse events will be monitored during each session, with researchers administering tDCS stimulation according to Brunoni et al.‘s protocol [23] to assess patient discomfort, pain, and any causality related to tDCS. Four treatment groups will be established:

Group A (tDCS-before-CCT): Patients will receive 20 minutes of tDCS, followed by 30 minutes of CCT after a 4-hour interval.Group B (tDCS-after-CCT): Patients will complete 30 minutes of CCT first, then will receive 20 minutes of tDCS after a 4-hour interval.Group C (tDCS-with-CCT): tDCS will be administered concurrently during the last 20 minutes of the 30-minute CCT session.Group D (CCT-only/Sham): Patients will undergo CCT with simultaneous placebo tDCS (sham stimulation).

Prior to the treatment intervention, patients will undergo a baseline assessment to determine eligibility. Enrollment will be based on the Montreal Cognitive Assessment (MoCA) [24]. Assessors will be blinded to group allocation. Post-treatment assessments will be conducted immediately after treatment completion, with follow-up assessments scheduled at 4 and 12 weeks post-treatment.The use of any non-invasive brain stimulation protocols other than those explicitly specified in this study (e.g., transcranial magnetic stimulation [TMS]) is strictly prohibited throughout the research period.

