### Study design

This is a single-center, double-blind, randomized controlled exploratory trial. Sixty patients will be randomly assigned to one of four groups (n = 15 per group). The protocol will be reported following Standard Protocol Items: Recommendations for Interventional Trials (SPIRIT) schedule statement(S1 File).Participant enrollment, randomization, assessment, and follow-up schedules are summarized in **Fig 1**.For a detailed visualization of the study workflow, **Fig 2**, which outlines the sequential steps from participant recruitment to final follow-up.

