### Blinding

Throughout the trial, participants, outcome assessors, and data analysts will remain blinded to group assignments until final database lock.Unblinding will be permitted solely under emergency circumstances (e.g., serious adverse events). No interim unblinding procedures are required, as all data analyses will be conducted following trial completion.

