### Optimizing retention and follow-up adherence

Participants will receive comprehensive information regarding trial procedures and expectations during the study period, with particular emphasis on the critical importance of follow-up compliance. A structured 3-month follow-up protocol will be provided to all patients,who will be strongly encouraged to attend scheduled clinic visits for face-to-face assessments. Two days prior to each follow-up appointment, designated research staff will proactively contact participants via telephone, WeChat, or alternative preferred communication channels to confirm attendance. For individuals unable to complete in-person evaluations, remote cognitive assessments will be facilitated through validated software platforms [https://doctor.shenzhenheling.com/],enabling flexible self-administration at the participant’s convenience. All remotely collected data will undergo immediate verification by research personnel, with subsequent outreach to be conducted as necessary to resolve missing or inconsistent responses. Participants retain the right to withdraw from follow-up procedures at any time without consequence to their standard medical care.

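### The trial is called double-blind with participants blinded to group, but sham is given only at the concurrent timing, so participants can be sham-blinded only for Group C versus Group D

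*Protocol article*

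**What the plan says.** The Study design section states: "This is a single-center, double-blind, randomized controlled exploratory trial". The Abstract uses the same label. The Blinding section does not use that term but makes the specific claim: "Throughout the trial, participants, outcome assessors, and data analysts will remain blinded to group assignments until final database lock".

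The Interventions section defines the four arms by when stimulation is given:

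- Group A: "Patients will receive 20 minutes of tDCS, followed by 30 minutes of CCT after a 4-hour interval".
- Group B: "Patients will complete 30 minutes of CCT first, then will receive 20 minutes of tDCS after a 4-hour interval".
- Group C: "tDCS will be administered concurrently during the last 20 minutes of the 30-minute CCT session".
- Group D: "Patients will undergo CCT with simultaneous placebo tDCS (sham stimulation".

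The Abstract confirms three stimulated arms and a single sham arm. The tDCS section describes sham as a 30-second activation after which the device switches off. Nothing in the article describes sham before or after training, or a scheme in which every arm has a device session at every time point.

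The Interventions section also says that assessors are blinded. The section on retention and follow-up adds that, for those who cannot attend in person, "remote cognitive assessments will be facilitated through validated software platforms", and goes on to say that participants take these tests themselves, when it suits them. The Secondary outcomes section places MoCA and MMSE at the 4- and 12-week follow-up.

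**The concern.** A patient can be blinded to group only if the schedule he or she experiences is compatible with more than one group. The arms here differ in something the patient observes directly: whether stimulation comes hours before training, during it or hours after it. Only the concurrent schedule is shared by an active and a sham arm.

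The stated primary objective is to compare timings, and MoCA is a primary outcome. MoCA is a performance test, so effort and expectation can affect it even when the assessor is blinded. If patients on different schedules hold different beliefs about their treatment, a between-schedule contrast mixes the effect of stimulation timing with the effect of belief. This arises after allocation, so randomization does not remove it, and the planned mixed model has no term that would.

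**Working it through.** No figure in the plan needs reproducing. The check is a count from the arm definitions.

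**Inputs.** 60 patients, 15 per group (Study design); arm schedules (Interventions); one sham arm (Abstract).

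**Probability that a session is active, given the schedule the patient sees**

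| Schedule | Groups | Active / total | Probability |
|---|---|---|---|
| tDCS 4 h before CCT | A | 15/15 | 1.0 |
| tDCS 4 h after CCT | B | 15/15 | 1.0 |
| tDCS during CCT | C and D | 15/30 | 0.5 |

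The two separated schedules together hold 15 + 15 = 30 patients. That is 30/60 = 50% of the sample and 30/45 = 67% of those on active stimulation.

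**Pairwise contrasts**

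| Contrast | Same timing? | P(active) on the two schedules |
|---|---|---|
| C-D | yes | 0.5 and 0.5 |
| A-B | no | 1.0 and 1.0 |
| A-C | no | 1.0 and 0.5 |
| B-C | no | 1.0 and 0.5 |
| A-D | no | 1.0 and 0.5 |
| B-D | no | 1.0 and 0.5 |

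One of six contrasts is matched on timing with sham as the comparator. Four of six compare unequal probabilities of active stimulation. Of the three active-versus-sham contrasts, only C-D is matched. Of the three timing contrasts, A-B has equal probabilities, while A-C and B-C do not.

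**What matching the sham would cost.** Suppose the 15 sham patients were spread evenly over the three timings. Each schedule would hold 15 active and 15/3 = 5 sham patients, so P(active) = 15/20 = 0.75 on every schedule with N still 60. The timing-matched contrast of C with sham would fall from 15 v 15 to 15 v 5. With equal variances, the ratio of standard errors is

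√[(1/15 + 1/5) / (1/15 + 1/15)] = √[(4/15)/(2/15)] = √2 ≈ 1.41.

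Pooling the sham patients restores n = 15 for the comparator but gives up the matching on timing.

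**Remote testing.** Set side by side, the Blinding and Interventions sections have follow-up cognition assessed by blinded assessors, while the retention section lets the patient self-administer the test. For those visits no blinded assessor gives the test, and a second mode of administration enters the same outcome.

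**The case against.** Seeing one's timing is certain; concluding that one is certainly on active stimulation is not. That conclusion requires patients to be told that sham exists only at the concurrent timing, and what patients are told is not shown. This stands, and it limits the claim to what patients are able to infer. It does not rescue the blinding statement: limited disclosure cannot hide the timing or make A and B look like D.

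A reader might infer that the bias favours A and B over both C and D. The documents do not support a direction. The 1.0 and 0.5 are allocation proportions; they measure neither belief nor MoCA points. The Discussion says that the investigators expect the synchronous strategy to do best. If that expectation reached patients, it would push towards C. It would also be too broad to say that the whole timing comparison is distorted, because A-B has equal probabilities. Assessors at in-person visits remain blinded, which narrows the route to effort and expectation.

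A reader might also tie the self-administered tests to patients in A and B. The option is open to every arm, is a fallback when attendance is impossible, uses platforms described as validated, and is followed by verification by research staff. The retention section does not name MoCA; the link comes from the follow-up schedule under Secondary outcomes. How often it will be used is unknown, and baseline testing and fNIRS are not affected. These facts make it a lesser and separate point. Staff verification deals with missing or inconsistent answers, though, not with who administered the test or whether the modes are equivalent.

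Finally, the trial is labelled exploratory and the certain defect is an overclaim. That argues for an inexpensive correction, not for leaving the claim in place.

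**Conclusion.** The point holds as a contradiction within the article. The Abstract and the Study design and Blinding sections claim participant blinding that the arm schedules cannot deliver beyond C versus D. It affects 30 of 60 patients and four of six contrasts, including two of the three comparisons with sham and two of the three timing comparisons. Those four may carry expectancy or effort bias of unknown size and direction. The count rests on the arms being delivered as described, with no unreported sham or double-dummy. Whether bias actually arises depends on what patients are told and believe.

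The conflict between self-administered follow-up tests and the blinded-assessor statements is real but smaller, and it applies equally to all arms.

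**What to change.** 1. In the Abstract and the Study design section replace the double-blind label, and in the Blinding section amend the sentence on participants, to read: *outcome assessors and data analysts blinded; participants sham-blinded for C versus D only*. This keeps the analyst blinding that the plan already states.
2. Report and interpret A or B versus C or D as not participant-blinded. Items 1 and 2 cost only wording and remain possible after enrolment has begun.
3. Optional, and only if built into the allocation list before the first patient: match sham to the separated timings. Each block of 12 has three sham places, so one per timing would fit without extra patients. The trade-off is the 1.41-fold standard error for the timing-matched C contrast, or a pooled sham that no longer matches on timing. Patients would still see their timing; only the probability of active stimulation would be equalised. The sponsor should weigh this openly and not treat it as a minor adjustment.
4. For remote follow-up in any arm, have an existing blinded assessor administer the test by video or telephone, record the mode of each assessment, and add a sensitivity analysis that excludes remote scores. This costs some assessor time, one data field and one additional analysis.

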To overcome these limitations, combining therapy with non-invasive brain stimulation has become a key research focus. Transcranial Direct Current Stimulation (tDCS) is especially prioritized due to its safety profile—it does not induce action potentials, which significantly reduces the risk of seizures and ensures treatment safety [13].Additionally, tDCS effectively modulates cortical excitability, addressing CCT’s limitations by regulating neuroplasticity in a targeted manner, thereby creating a ‘neuroactivation-cognitive enhancement’ feedback loop [14,15].tDCS also exhibits significant long-lasting aftereffects, with 20–30 minutes of stimulation maintaining neural network modulation for up to 90 minutes post-treatment, thereby providing a neurobiological basis for sustained cognitive enhancement [16].However, most devices lack real-time monitoring and adaptive parameter adjustments (e.g., stimulus intensity), which limits their regulatory efficacy beyond simple intervention-based stimulation.

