#### tDCS.

The MBM-1 intelligent electrostimulator (Jiangxi Huaheng Jingxing Medical Technology Co., Ltd.) will be used, with 4.5 × 5.5 cm isotonic gelatin sponge electrodes soaked in saline (0.9% NaCl). Stimulation will target the dorsolateral prefrontal cortex (DLPFC) based on the EEG 10–20 system, with F3 as the anode and F4 as the cathode (**Fig 3**). Parameters: 1 mA current intensity (selected for safety and demonstrated behavioral effects) [25].Each session will last 20 minutes, with 5 sessions per week for 2 weeks.Ramp-Up/Ramp-Down: The current will gradually increase to 1 mA over the first 30 seconds and decrease to 0 mA during the final 30 seconds of each session. For sham stimulation, the device will activate for 30 seconds before automatically shutting down.

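### The immediate post-treatment assessment has no common interval from the last stimulation, so the between-arm comparison at that visit may mix a transient after-effect with the lasting effect of timing

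*Protocol article*

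**What the plan says.** The Interventions section sets the timing of the visit: "Post-treatment assessments will be conducted immediately after treatment completion, with follow-up assessments scheduled at 4 and 12 weeks post-treatment". The article gives no minimum delay, no window and no common reference point for the arms.

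The same section defines the daily order in each arm:

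- Group A: "Patients will receive 20 minutes of tDCS, followed by 30 minutes of CCT after a 4-hour interval". Training comes last.
- Group B: "Patients will complete 30 minutes of CCT first, then will receive 20 minutes of tDCS after a 4-hour interval". Stimulation comes last.
- Group C: "tDCS will be administered concurrently during the last 20 minutes of the 30-minute CCT session". Both end together.
- Group D: training with simultaneous sham. The tDCS section says the sham device switches off after 30 seconds.

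On how long stimulation acts, the Introduction cites an after-effect "with 20–30 minutes of stimulation maintaining neural network modulation for up to 90 minutes post-treatment". The tDCS section puts the trial within that range: "Each session will last 20 minutes, with 5 sessions per week for 2 weeks".

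On what is measured at this visit, the article is uneven. The Introduction says fNIRS will "dynamically monitor pre- and post-treatment hemodynamic parameters in the prefrontal cortex", and Outcome measures lists fNIRS prefrontal activation with MoCA as primary. Sample size estimation counts a post-treatment MoCA among three measurements. The primary and secondary outcome paragraphs list MoCA and MMSE at baseline, 4 weeks and 12 weeks only.

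**The concern.** The primary objective is to compare the orders in which tDCS and training are combined. If the test follows session 10 directly, the order also decides how long after stimulation, and how long after training, the patient is tested. A short-lived change in prefrontal oxygenation or test performance in the arms that end on stimulation could then be read as an effect of better timing.

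Randomisation does not remove this, because the allocated arm itself sets the lag. Assessor blinding does not remove it, and neither does covariate adjustment in the mixed model. After data collection, arm and lag cannot be separated at that visit. For fNIRS the visit matters most, because the article names no later fNIRS reading: the repeats at 4 and 12 weeks are described for MoCA and MMSE only.

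**Working it through.** **Inputs.** Session orders and the 4-hour (240-minute) interval come from Interventions; the 20-minute stimulation from Interventions and the tDCS section; 30-minute training from Interventions and the CCT section; the after-effect of up to 90 minutes from the Introduction. The article states no lag of its own to reproduce.

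**Lags on the literal reading.** Lag = end of the last component minus end of the component in question. Time 0 is the start of the day's first component.

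| Arm | tDCS (min) | CCT (min) | Test at | Since tDCS ended | Since CCT ended |
|---|---|---|---|---|---|
| A | 0–20 | 260–290 | 290 | 290 − 20 = 270 | 0 |
| B | 270–290 | 0–30 | 290 | 0 | 290 − 30 = 260 |
| C | 10–30 | 0–30 | 30 | 0 | 0 |
| D | sham only | 0–30 | 30 | no sustained current | 0 |

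B and C fall inside the 90-minute figure; A is 270 − 90 = 180 minutes past it. The fNIRS run takes 8 min + (30 + 60 + 75) s = 10.75 min, so in B and C it fits inside the 90 minutes.

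**What a transient shift could do (illustration only).** Assume no lasting difference between arms, a shift of b SD in B and C equally and none in A and D, 15 per arm, two-sided 5% level, and a comparison at this single visit.

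- A versus C: noncentral t, 28 df, noncentrality b·√(15/2). For b = 0.3, 0.5 and 0.8 this is 0.82, 1.37 and 2.19.
- Four-arm F test: 3 and 56 df, arm means 0, b, b, 0, noncentrality 15·4·(b/2)² = 15b². This is 1.35, 3.75 and 9.6.
- Ranking of the three active arms: simulated arm means with standard error SD/√15.

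| b (assumed) | A vs C significant | Omnibus F significant | A ranked last | C ranked first |
|---|---|---|---|---|
| 0.3 SD | 12.5% | 13.5% | 68% | 45% |
| 0.5 SD | 26% | 32% | 85% | 49% |
| 0.8 SD | 56% | 71% | 97% | 50% |

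With no shift, the first two columns would be 5% and the last two 33%. Nothing in the article supports a particular b, its sign, or equality between B and C. The rates apply to the comparison at an individual time point described in Statistical methods, not to the group × time mixed model.

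**After the fix.** With every arm tested 24 hours after its last component, the time since tDCS is 24 + 4.5 = 28.5 hours in A and 24 hours in B and C. All are far beyond 90 minutes.

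**The case against.** The strongest reply is that the treatment in question is the two-week course, and that the word immediately is set against 4 and 12 weeks. It may mean an end-of-course visit on a later day, not minute zero after session 10. The schedule figure is not visible in the text at hand, and visit windows are often left to a full protocol. This stands in part: the lags above describe the rule followed to the letter, not a known practice. But nothing shown requires a delay, and a site that tests straight after session 10 complies with the wording.

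The second reply concerns scope, and it stands. The 4- and 12-week visits are far outside the after-effect. On the schedule in Outcome measures, neither MoCA nor MMSE is taken at the immediate visit at all.

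The third concerns size, and it also stands. The 90 minutes is an upper bound and refers to neural network modulation, not to MoCA points or task-related oxygenation. The training lag is unequal as well: fatigue or practice straight after 30 minutes of training, present in A, C and D but not in B, could add to a stimulation after-effect or offset it.

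A reader might infer that the design favours the authors' hypothesis that concurrent stimulation is best. The documents do not support that. B and C have the same lag from stimulation; under an equal shift, C ranks first in only 45% to 50% of trials, and B does so equally often. The shift disadvantages A without lifting C above B. Nor can one infer that the trial's timing comparison as a whole is confounded; only the immediate visit is exposed.

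**Conclusion.** The point holds for the immediate post-treatment visit. As written, the time from the end of tDCS to the test can differ by 270 minutes between A and the other two active arms, and the time from training to the test by 260 minutes between B and the rest, against a stated after-effect of up to 90 minutes. The between-arm comparison at that visit may therefore combine a transient stimulation or training after-effect with the lasting effect of timing.

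It bears mainly on fNIRS. It bears on MoCA and MMSE only if a post-treatment test is held, which Sample size estimation and Interventions imply and Outcome measures does not list. Comparisons at 4 and 12 weeks are not affected.

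The size and direction of any bias cannot be derived from the article. If the after-effect is a benefit, it would disadvantage A and D relative to both B and C. The conclusion rests on the literal reading of the visit rule and on the article's own after-effect figure; the error rates above are illustrations under assumed shifts. Since the trial calls itself exploratory and only one visit is involved, this should be fixed but does not undermine the design.

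**What to change.** 1. Replace the immediate assessment with one window, identical in all arms, that starts well beyond 90 minutes after the last tDCS or training component: for example, the next available day, before any other therapy that day.
2. Record the clock times of the last tDCS, the last training session and each test.
3. Reconcile the MoCA and MMSE schedule across Sample size estimation, Interventions and Outcome measures, so that it is clear whether a post-treatment test is held.

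No treatment changes. The cost is protocol wording, one short extra attendance for outpatients and a later post-treatment reading. If the five weekly sessions run Monday to Friday (an assumption), session 10 falls on a Friday and a next-working-day visit comes about three days later; otherwise the delay is about one day. The article says data collection had not begun at submission. A change made before the first post-treatment visit loses no data.
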